### Ground truth diagnosis

Patients will be classified into whether they have benign or malignant nodules as follows:

Benign-nodule patients:By resolution or stability of all qualifying incidental pulmonary nodules as determined from volumetry-based measurement on imaging follow-up over 12 months.By histopathology from biopsy or surgery of all qualifying incidental pulmonary nodules (within 12 months of baseline CT scan).Malignant-nodule patients:By histopathology from biopsy or surgery (within 12 months of baseline CT scan) of at least one qualifying incidental pulmonary nodule.Probable benign-nodule patients:By resolution, stability or shrinkage of qualifying incidental pulmonary nodules that are not in ground-truth outcomes #1 or #2 above as determined from volumetry-based measurement on imaging follow-up conducted between 3 and 12 months after the baseline CT scan.By resolution, stability or shrinkage of qualifying incidental pulmonary nodules that are not in ground-truth outcomes 1 or 2 above as determined from diameter-based measurement on imaging follow-up conducted 12 months after the baseline CT scan (supplemented with a volume-based measurement of the nodule that will be performed for research purposes).Probable malignant-nodule patients:By clinical diagnosis of lung cancer, in whom a biopsy or resection is not possible, based on high clinical probability and who are registered at a lung cancer MDT/and/or receive non-surgical treatment (stereotactic ablative radiotherapy (SABR)/radiotherapy/microwave ablation).

Volumetry-based measurement of nodule stability—and hence a benign diagnosis—will be satisfied if the lung nodule volume on the follow-up CT scan was <125% of the lung nodule volume on the baseline CT scan.

If the standard care at a particular site does not incorporate volumetry-based measurements, the volumetric measurement will be applied as part of the research study to the relevant follow-up CT scans.

Any lung nodule patients who do not fall into either of the two ground-truth outcomes 1 or 2 above will be considered to have an indeterminate diagnosis at the time of analysis and will be analysed with and without the inclusion of the ground-truth outcomes in 3 and 4.

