### Outcome measures

The outcome measures for the primary and secondary objectives are outlined in table 1.

**Table 1 T1:** Study objectives and outcome measures

Objective	Outcome measure
Primary: Determine the potential effect of the LCP on discharge	The measured difference between standard care and the three LCP-based options described under AI model for: No and percentage of cancer patients discharged (straight after assessment of the baseline scan). No and percentage of benign-nodule patients discharged (straight after assessment of the baseline scan).
Secondary: Determine the potential effect of the LCP on possible adherence to clinical guidelines	The measured difference between standard care and the three LCP-based options described under AI model: No and percentage of patients for whom a validated risk model (Brock or LCP) is used to guide the next clinical management step (ie, counting the instances where Brock is not used or where LCP is not possible to compute, or it is ignored).
Secondary: Determine the potential effect of the LCP on overall clinical management, as well as scan and procedure utilisation	No and percentage of cancer patients for whom there would have been a change in clinical management according to each of the three LCP-based options described under AI model compared with actual care (correctly for more aggressive management and incorrectly for less aggressive management). No and percentage of benign-nodule patients for whom there would have been a change in clinical management according to each of the three LCP-based options described under AI model compared with actual care (incorrectly by more aggressive management and correctly for less aggressive management). The measured difference between standard care and the three LCP-based options described under AI model for: No and percentage of CT scans and PET/CT scans performed on benign-nodule patients. No and percentage of non-surgical biopsies performed on benign-nodule patients. No and percentage of surgical excisions on benign-nodule patients.

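### A lung cancer treated without histology can meet both the benign rule (outcome 1) and the probable-malignant rule (outcome 4), and the text as written favours benign

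*Protocol article*

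**What the plan says.** The Protocol article, section Ground truth diagnosis, lists four classes, which its closing sentence refers to by number.

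- Outcome 1, benign, imaging route: "By resolution or stability of all qualifying incidental pulmonary nodules as determined from volumetry-based measurement on imaging follow-up over 12 months". A separate paragraph equates passing the volume test with a benign label: "Volumetry-based measurement of nodule stability—and hence a benign diagnosis—will be satisfied". The test itself is only a ceiling on growth, met when "lung nodule volume on the follow-up CT scan was <125% of the lung nodule volume on the baseline CT scan".
- Outcome 2, malignant: "By histopathology from biopsy or surgery (within 12 months of baseline CT scan) of at least one qualifying incidental pulmonary nodule".
- Outcome 3, probable benign: resolution, stability or shrinkage on volumetry between 3 and 12 months, or on diameter at 12 months, for nodules not already in outcomes 1 or 2.
- Outcome 4, probable malignant: "By clinical diagnosis of lung cancer, in whom a biopsy or resection is not possible, based on high clinical probability", where the patient is registered at a lung cancer MDT and/or is one of those who "receive non-surgical treatment (stereotactic ablative radiotherapy (SABR)/radiotherapy/microwave ablation".

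The closing sentence then covers "Any lung nodule patients who do not fall into either of the two ground-truth outcomes 1 or 2 above". These patients are indeterminate, and the analysis is run with and without outcomes 3 and 4.

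In Table 1, the primary outcome measures include "No and percentage of cancer patients discharged (straight after assessment of the baseline scan" and the matching count and percentage for benign-nodule patients.

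**The concern.** The imaging route to a benign label has no condition that the nodule was left untreated or that no cancer was diagnosed clinically. Local treatment aims to stop growth, so a treated cancer may well be no larger at 12 months. The test that is meant to show benign behaviour may then be showing a treatment effect.

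The reference standard decides which primary measure a patient counts towards. A cancer filed as benign enlarges the benign denominator, and its CT and PET/CT scans become scans on benign-nodule patients in the secondary outcomes. If LCP alone would have discharged that patient, a missed cancer is scored as a benign patient discharged. The error would mainly favour LCP, because a patient who went on to cancer treatment is unlikely to have been discharged at baseline under standard care.

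**Working it through.** **Rule check.** No figure in the article bears directly on this point, so the check is to apply the written rules. Take a patient with a clinical lung cancer diagnosis, no histology, local treatment soon after baseline, and volumetric follow-up.

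| Situation | Outcome 1 | Outcome 2 | Outcome 3 | Outcome 4 | Class as written |
|---|---|---|---|---|---|
| 12 months, resolved | met | no tissue | excluded by 1 | met | benign |
| 12 months, volume 100% or 124% of baseline | met | no tissue | excluded by 1 | met | benign |
| 12 months, volume 60% of baseline | met only through the 125% test | no tissue | excluded if 1 is met | met | benign, on that reading |
| 12 months, volume 125% or more | not met | no tissue | not met | met | probable malignant |
| Last scan at month 6, shrunken or stable | 12 months not reached | no tissue | met | met | undefined |

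- In the first three rows outcomes 1 and 4 overlap. The closing sentence opens outcomes 3 and 4 only to patients outside 1 and 2, so outcome 1 prevails.
- The third row depends on the 125% test having no lower bound, because outcome 1 names resolution and stability while outcome 3 adds shrinkage. The first two rows do not depend on it.
- In the last row, outcome 3 excludes only outcomes 1 and 2, and nothing ranks 3 against 4.
- The analysis with and without outcomes 3 and 4 cannot correct the first three rows, because those patients are held in outcome 1.

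**Size.** Inputs from the article: 2000 patients (Design and setting), and 0.4% of cancers discharged by the LCP threshold but retained by the Brock threshold that stands for standard care (Sample size). Two inputs are not in the article and are assumed: 5% to 15% of patients have cancer, and 10% to 20% of cancers are treated without tissue.

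- Cancers: 2000 × 0.05 = 100 to 2000 × 0.15 = 300.
- Treated without tissue: 100 × 0.10 = 10 to 300 × 0.20 = 60. This is an upper limit on misfiling, since not all will be below 125% at 12 months.
- Share of the benign group if all are misfiled: 10 / (1900 + 10) = 0.5% to 60 / (1700 + 60) = 3.4%.
- LCP-only discharged cancers in the whole study: 0.004 × 100 = 0.4 to 0.004 × 300 = 1.2.
- Of these, open to misfiling: 0.004 × 10 = 0.04 to 0.004 × 60 = 0.24, if the 0.4% applies equally to this subgroup.

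With wider assumptions (5% to 20% cancers; 5% to 30% of them treated without tissue and below 125%), the last figure runs from 0.004 × 100 × 0.05 = 0.02 to 0.004 × 400 × 0.30 = 0.48.

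**Effect of one case.** With 200 cancers and 3 discharged, moving one patient changes the rate from 3/200 = 1.50% to 2/199 = 1.01%. The planned conditional logistic regression estimates the odds ratio from the two discordant counts. If the LCP-only count falls from 1 to 0, there is no finite odds ratio and no usable Wald test, and no LCP-only missed cancer is reported.

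**The case against.** The strongest reply is that outcome 4 exists for exactly these patients, so the intent is plain and no one would file a treated cancer as benign. The precedence is partly inferred too: only outcome 3 carries an explicit exclusion, and the closing sentence says how patients outside 1 and 2 are handled, not that a treated cancer is benign. The article is also a condensed account, and a full protocol could contain a tie-break. The intent is indeed clear, but it is not what the rule says. The article states the volume test, equates passing it with a benign diagnosis, and confines outcomes 3 and 4 to the remaining patients. This is a stated rule that misclassifies, not an omitted detail.

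On size, the objection largely stands. A reader might infer that one or two misfiled patients would change the result. That holds only if a misfiled patient is also discordant. A treated cancer that neither standard care nor LCP discharged adds nothing to the paired odds ratio; it only shifts denominators. Outcome 4 also requires high clinical probability, which makes an LCP discharge less likely in this group.

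Two other inferences go too far. A reader might conclude that these patients' cancer treatment is counted as over-management of benign nodules, but the Table 1 utilisation counts for benign-nodule patients cover CT and PET/CT scans, non-surgical biopsies and surgical excisions, not SABR, radiotherapy or ablation. A reader might also blame this gap alone for their absence from the cancer group, but outcome 4 patients are absent by design from the analysis without outcomes 3 and 4.

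**Conclusion.** The overlap is real and should be reconciled; severity is moderate. As written, an unbiopsied, treated cancer that is stable or resolved at 12 months is definite benign, and one with only an earlier scan has two conflicting probable labels. A shrunken nodule at 12 months is definite benign only if the 125% test is read without a lower bound.

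The certain effect is contamination of the benign group, at most about 0.5% to 3.4% under the assumed 5% to 15% cancers and 10% to 20% treated without tissue. The serious effect, a missed cancer scored as a benign discharge, has an expected count of about 0.04 to 0.24, well below one. It still deserves attention because the cell it would alter is expected to hold only 0.4 to 1.2 patients. The documents do not support a claim that the primary result is likely to be overturned.

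**What to change.** Reconcile the classes in Ground truth diagnosis with wording such as: imaging-based outcomes 1 and 3 apply only to nodules with no clinical lung cancer diagnosis and no cancer-directed treatment before the deciding scan; outcome 4 takes precedence over imaging-based outcomes 1 and 3; histology decides wherever it exists.

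This changes neither care nor data collection, since the Data collection section already records treatments and the final nodule diagnosis. The cost is that a few patients leave definite benign and join the cancer group only in the analysis that includes outcomes 3 and 4. In the analysis without them, they are in neither group. Reporting how many patients the precedence rule moves, and how many of them each LCP option would have discharged, would show whether it mattered.

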In line with Standard Protocol Items: Recommendations for Interventional Trials - Artificial Intelligence (SPIRIT-AI) guidelines, performance errors that would have happened if the LCP or LCP-guided decision-making were part of standard care will be analysed and reported as outcome measures for the primary objective of this study.

Evaluation of LCP as threshold-based tests (scenarios #2 and #3 as described under AI model), which require access to LCP-CNN values, will be performed as a batch at the end of the study follow-up period. The threshold will be defined prospectively based on values from training datasets of similar patient populations. The use of the recommendation with physicians making the decision will be evaluated via a separate research meeting at the end of the 12-month follow-up period.

For cost-effectiveness modelling, quality of life data will be collected by inviting patients to complete an EQ-5D-5L quality of life questionnaire at two time points: (a) as close as possible to the baseline CT scan on which their pulmonary nodule was detected and (b) at a 1-year time point afterwards. A participant diary about primary care usage will also be collected at the 1-year mark.

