## Ethics and dissemination

This study has been reviewed and given a favourable opinion by the South Central—Oxford C Research Ethics Committee in UK (REC reference number: 22/SC/0142).

Given the study’s observational nature, we do not envisage any elevation to the harms or the risk of harm for patients. The sponsor and chief investigator have conducted a full risk assessment.

Patients will be asked to give their consent to participate in the study (including the analysis of standard-care CT scans, associated data collection and the healthcare economics assessment) by telephone or face to face when attending routine clinic appointments. No additional patient visits, scans or procedures are planned for the study. Patients not wishing to participate in the health economics assessment may still participate in the study’s CT imaging analysis.

The findings of this study will be shared with the funder (NHS Accelerated Access Collaborative). Results will be presented at academic and clinical conferences. The study will result in at least one peer-reviewed publication of the findings in an international medical journal.

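### Ground truth comes mainly from follow-up that standard care itself decides on, so standard-care discharges at baseline are under-counted in both primary comparisons, to a degree the plan does not fix

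*Protocol article*

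**What the plan says.** Table 1 of the Protocol article (Outcome measures) gives two primary measures, each compared between standard care and the three LCP options: "No and percentage of cancer patients discharged (straight after assessment of the baseline scan") and "No and percentage of benign-nodule patients discharged (straight after assessment of the baseline scan"). Each can be counted only in patients whose nodule status is known.

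The section Ground truth diagnosis sets four categories:

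- Benign: either "By resolution or stability of all qualifying incidental pulmonary nodules as determined from volumetry-based measurement on imaging follow-up over 12 months" or "By histopathology from biopsy or surgery of all qualifying incidental pulmonary nodules (within 12 months of baseline CT scan").
- Malignant: "By histopathology from biopsy or surgery (within 12 months of baseline CT scan) of at least one qualifying incidental pulmonary nodule".
- Probable benign: follow-up imaging at 3 to 12 months by volume, or at 12 months by diameter.
- Probable malignant: a clinical lung cancer diagnosis where tissue cannot be obtained.

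Patients outside the first two categories "will be considered to have an indeterminate diagnosis at the time of analysis", and the analysis is run with and without the third and fourth.

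Three further statements decide who can reach a label. Clinical pathway anticipates no change to standard care. Data collection takes follow-up images from the patient's own nodule follow-up. Ethics and dissemination states: "No additional patient visits, scans or procedures are planned for the study".

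**The concern.** The comparator's own decision largely determines whether the reference standard is obtained. A patient whom standard care discharges at baseline leaves nodule follow-up, and no research scan replaces it. A patient whom only LCP would have discharged is followed up as usual and normally reaches a label. This is differential verification, and it falls on one of the two discordant cells from which a paired analysis takes its whole estimate.

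The two primary results are distorted in opposite directions. Correct benign discharges by standard care drop out, which flatters LCP. Cancers that standard care discharges and LCP would have kept are seen only if they are diagnosed within 12 months, which hides LCP's advantage. Neither result can be called conservative overall. The Introduction says the study is meant to inform whether LCP should become the standard of care, so the distortion bears directly on that decision.

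**Working it through.** **Inputs from Sample size.** Benign discordance: LCP-only discharge 17.0%, Brock-only discharge 13.5%, OR 1.26, 2026 patients for 80% power. Cancer discordance: LCP-only discharge 0.4%, Brock-only discharge 2.6%, 659 patients for 90% power. The plan takes the Brock threshold to represent standard care.

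**Assumed inputs.** v_SC and v_LCP are the shares of the standard-care-only and LCP-only discharge cells that obtain a ground truth. The documents give neither, so ranges are shown. The number of benign patients before any loss is taken as 1600.

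**Step 1: the plan's own figures.** 17.0/13.5 = 1.26, as stated. McNemar sample size, two-sided 0.05: n = [1.96√(p1+p2) + z√(p1+p2−d²)]²/d².

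- Cancer: p1+p2 = 0.030, d = 0.022, z = 1.282, so n = 648 against 659.
- Benign: p1+p2 = 0.305, d = 0.035, z = 0.842, so n = 1952 against 2026. The exact conditional test at 2026 has 80.4% power.

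The figures are close enough that the arithmetic is not the problem. It does, however, treat both discordant cells as fully observed.

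**Step 2: who reaches a label.**

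| Standard care | LCP option | Route to ground truth |
|---|---|---|
| Discharge | Keep | Incidental only: unrelated imaging, cancer diagnosed within 12 months, management modified after the LCP score |
| Keep | Discharge | Ordinary follow-up; mostly classified |
| Keep | Keep | Ordinary follow-up; mostly classified |
| Discharge | Discharge | Incidental only; does not enter the paired OR but changes the percentages |

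Adding the third and fourth categories does not restore the first row: the third also needs imaging and the fourth needs a cancer diagnosis.

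**Step 3: benign OR.** Observed OR = (17.0 × v_LCP)/(13.5 × v_SC) = 1.26 × v_LCP/v_SC.

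| v_LCP | v_SC | Observed OR |
|---|---|---|
| 1 | 1 | 1.26 |
| 1 | 0.75 | 1.68 |
| 1 | 0.50 | 2.52 |
| 0.8 | 0.50 | 2.01 |

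**Step 4: benign percentages.** With v_SC = 0.5, v_LCP = 1 and no patients discharged by both, the classified fraction is 1 − 0.5 × 0.135 = 0.9325. Standard care then appears to discharge 6.75/93.25 = 7.2% and LCP 17.0/93.25 = 18.2%. The difference is 11.0 points instead of 3.5.

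**Step 5: false significance with no true difference.** Take 13.5% each way in 1600 benign patients before loss, with v_LCP = 1. The expected LCP-only count is 216.

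- v_SC = 0.9: standard-care-only 194.4; z = (216 − 194.4)/√410.4 = 1.07. A significant result for LCP occurs in about 18% of trials (0.185 by simulation with the Wald test).
- v_SC = 0.75: standard-care-only 162; z = (216 − 162)/√378 = 2.78; about 79% of trials.

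The nominal rate in that direction is 2.5%.

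**Step 6: cancer ratio.** The planned ratio of standard-care-only to LCP-only discharges is 2.6/0.4 = 6.5. With v_LCP = 1 it becomes 6.5 × v_SC: 3.25 at v_SC = 0.5 and 1.62 at 0.25. It reaches 1 at v_SC = 0.4/2.6 = 0.154. The value of v_SC among cancers need not equal that among benign patients.

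**The case against.** Some discharged patients will be classified. Data collection lets the team modify management after seeing the LCP score, and in the first scenario (physician guided by the integer score) that could return to follow-up exactly the patients whom standard care alone would discharge. A cancer diagnosed within 12 months also earns a label. This stands: a reader might infer that the standard-care-only cell is empty, and the documents do not support that. The routes are nevertheless selective. Modification depends on the very score under test, Clinical pathway anticipates no change of care, and the two threshold scenarios are evaluated only after follow-up has ended.

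The illustration also leans on strong inputs. Setting v_LCP = 1 is the extreme case: a nodule that grows without histology or a clinical diagnosis, or a patient without a scan in the window, is indeterminate too. The 17.0% and 13.5% are disagreements between two model thresholds, not discharge rates under actual care. Both points stand, so the figures show how sensitive the result is; they do not forecast the bias.

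The full protocol or SAP might add a source such as registry linkage. The classification rules printed here use none, and they already specify a sensitivity analysis that leaves this group out. Nor does the article say outright that indeterminate patients are dropped; but a patient with no label cannot be counted in either a benign or a cancer denominator.

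**Conclusion.** The concern holds. Under the printed ground-truth rules, standard-care discharges at baseline are classified less often, and more selectively, than LCP-only discharges. Both primary comparisons are biased as a result: the benign one in favour of LCP, the missed-cancer one against it. The planned analysis with and without the probable categories does not correct this.

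The direction rests on v_SC being lower than v_LCP, which follows from unchanged care and the absence of added scans. The size rests on values the documents do not give. On the plan's discordances with v_LCP = 1, losing a quarter of the standard-care-only cell is enough to move the OR from 1.26 to 1.68, and losing a tenth raises the false-positive rate for LCP about sevenfold (18% against 2.5%).

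A reader might go further and conclude that neither primary question can be answered. The documents do not support that: the loss is partial and unknown, and it can be counted and bounded.

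**What to change.** 1. Report the number of indeterminate patients cross-classified by standard-care decision and by each LCP option's decision.
2. For both primary outcomes, accompany the classified-only analysis with two-sided bounds. At one extreme, count all unverified standard-care discharges as benign; at the other, count them as malignant at a plausible rate stated in advance. State that the primary conclusion is not drawn from the classified-only analysis alone.
3. At 1 year, record from hospital and lung cancer MDT records whether lung cancer was diagnosed in each patient discharged at baseline. Use the absence of a recorded cancer as a separate, softer category in a sensitivity analysis, and state that it misses cancers that have not yet presented. It should not enter the main set, where such cancers would count as correct discharges by standard care.
4. Report the BTS-compliant comparison, which Data collection already intends, alongside the primary discharge outcomes, restricted or bounded in the same way.

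Cost: no scans or visits. The record check is a new site task. The planned 1-year contact is a questionnaire and a diary ("A participant diary about primary care usage will also be collected at the 1-year mark"), and patients may decline the health economics part, so it cannot stand in for the check. The analysis grows a little, and the conclusions will be wider and less favourable.

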### Study population

Patients who have undergone CT that has detected a pulmonary nodule and was performed for a reason other than suspicion of lung cancer will be reviewed for study eligibility (box 1).

Box 1Patient eligibility criteriaInclusion criteriaPatients aged 35 years or over.Patients with a baseline CT study with at least one incidentally detected solid or part-solid pulmonary nodule that is 5–30 mm in maximum axial diameter for the whole lesion, measured using manual electronic callipers, and that is not fully calcified. The solid component of the part-solid nodule must be ≥80% of the total nodule size.Patients with a baseline CT study which includes at least one series with acquisition parameters which meet Virtual Nodule Clinic requirements.The patient has a baseline CT study that includes at least one series that comprises at least one full-inspiration breath-hold scan without a high degree of contrast media and does not exhibit quality issues (eg, motion artefacts).Exclusion criteriaPatients who received a diagnosis of cancer in the last 5 years.Patients who have thoracic implants that adversely impact the imaging appearances of the nodule.Patients who have more than five reported pulmonary nodules of any size or type, excluding fully calcified nodules (a marker of prior granulomatous infection) or metastatic lung cancer.Patients who have one or more additional nodules that are already undergoing follow-up according to pulmonary nodule management standard care.Patients who have one or more additional nodules that are pure ground glass opacity of 5 mm in maximum axial diameter for the whole lesion measured using manual electronic callipers.Patients who have one or more additional nodules >30 mm in maximum axial diameter for the whole lesion measured using manual electronic callipers.Patients with part-solid nodules where the solid component is <80% of the total nodule size.

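### A multi-nodule patient whose nodules are shown benign by different accepted methods (histology for one, 12-month volumetry for the rest) meets neither definite-benign rule

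*Protocol article*

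**What the plan says.** The Protocol article, under Ground truth diagnosis, classifies patients, not nodules: "Patients will be classified into whether they have benign or malignant nodules as follows". Two routes lead to the definite benign class:

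- Imaging: "By resolution or stability of all qualifying incidental pulmonary nodules as determined from volumetry-based measurement on imaging follow-up over 12 months".
- Histology: "By histopathology from biopsy or surgery of all qualifying incidental pulmonary nodules (within 12 months of baseline CT scan".

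A definite malignant diagnosis needs histology on at least one qualifying nodule. The section then makes indeterminate the default class, in a sentence that opens "Any lung nodule patients who do not fall into either of the two ground-truth outcomes 1 or 2 above will be considered to have an" and ends by naming that class. These patients "will be analysed with and without the inclusion of the ground-truth outcomes in 3 and 4", which are the probable benign and probable malignant classes.

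Patients with several nodules are eligible. Box 1 asks for at least one qualifying nodule and sets an upper limit by excluding "Patients who have more than five reported pulmonary nodules of any size or type". Table 1 uses the benign class as the denominator for one of the two primary discharge outcomes. It uses it again for secondary outcomes that include "No and percentage of surgical excisions on benign-nodule patients" and thoracic, respiratory or vascular events within 30 days of a procedure.

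**The concern.** The condition on all nodules sits inside each route separately, so proof cannot be pooled across routes. Suppose one nodule is excised and benign and the second is stable by volumetry at 12 months but was never sampled. The imaging route fails because the excised nodule has no 12-month volume. The histology route fails because the second nodule has no histology. Nothing is malignant. The rule makes the patient indeterminate, although each nodule was settled by a method that the plan treats as definitive.

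The patients affected are not a random subset. They enter this gap because they had a procedure on some nodules and not on others. The definite-benign analysis then leaves out the very patients in whom a benign excision, or a complication of a procedure, is to be counted.

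**Working it through.** The point concerns classification logic, and the documents give no figure for it to reproduce. The check is an enumeration of two-nodule patients against the stated rules.

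Nodule states:

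- A: benign histology, no 12-month volume (excised, or biopsied and not followed by volumetry)
- B: benign histology, left in place and stable on 12-month volumetry
- C: stable on 12-month volumetry, no histology

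| Pair | Imaging route (all) | Histology route (all) | Class as written | Each nodule by either route |
|---|---|---|---|---|
| A + A | fails | met | benign | benign |
| A + B | fails | met | benign | benign |
| A + C | fails | fails | indeterminate | benign |
| B + B | met | met | benign | benign |
| B + C | met | fails | benign | benign |
| C + C | met | fails | benign | benign |

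Only A + C changes class. A resolved nodule satisfies the imaging route just as a stable one does, so it can replace C without changing the result.

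**Where A + C goes next.** The volumetric route to probable benign accepts resolution, stability or shrinkage between 3 and 12 months and does not repeat the word all. The C nodule can therefore carry the patient into that class and so into the analysis that includes the probable classes. The patient remains outside the definite-only analysis.

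**Effect on procedure outcomes in the definite-only analysis.** Let n be the patients classed as definite benign, e of them with the procedure in question, and m the A + C patients who had that procedure. The count should be e + m but is reported as e. The percentage should be (e + m)/(n + m) but is reported as e/n. The difference is

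(e + m)/(n + m) − e/n = m(n − e) / [n(n + m)],

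which is positive whenever e < n. Both the count and the percentage are thus too low. For 30-day events the count can only fall or stay the same, since an affected patient need not have had an event. The documents give none of n, e or m.

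**Effect on the primary benign comparison.** Inputs from Sample size: discordant proportions 17.0% and 13.5%, 2026 individuals, 80% power. With d = 0.170 − 0.135 = 0.035 and s = 0.170 + 0.135 = 0.305, the normal-approximation McNemar size is

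n = [1.96√s + 0.842√(s − d²)]² / d² = 1952,

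or about 2009 with a continuity correction, against the stated 2026. Power at a given n is Φ{(d√n − 1.96√s)/√(s − d²)}. The losses below are assumed, for illustration only:

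| Assumed loss from 2026 | n | Power |
|---|---|---|
| 0% | 2026 | 81.4% |
| 1% | 2006 | 81.1% |
| 2% | 1985 | 80.7% |
| 5% | 1925 | 79.5% |

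This treats the loss as random across pairs. In fact a patient who went on to excision will usually not have been discharged at baseline under standard care. If the LCP option would not have discharged the patient either, the pair is concordant and carries no information on the OR in conditional logistic regression. Only affected patients whom the LCP option would have discharged could change the OR.

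**The case against.** The other side has four arguments.

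- Biopsy commonly leaves the nodule in place. If that nodule and the rest are stable at 12 months, the imaging route is met (B + C in the table). This stands. A reader might infer that nearly every benign multi-nodule patient with a procedure on only some nodules is lost; the rules do not support that.
- The plan also runs an analysis that includes the probable classes, which can bring the patient back. This stands too, so it would be wrong to say that the patient is lost altogether. It does not remove the problem. Probable benign is meant for weaker evidence, and comparing the two analyses would mix real diagnostic uncertainty with an artefact of wording.
- The number affected needs several conditions at once: two or more qualifying nodules, a benign procedure without a 12-month volume, at least one nodule unsampled, and the unsampled nodules stable or resolved. The limit of five in Box 1 counts nodules of any size or type, not only qualifying ones. A reader might take the share of multi-nodule patients as the share of benign procedures lost; the documents give neither figure, and the first would not yield the second.
- The article is condensed, and mixed evidence may be dealt with in the full protocol. This carries less weight. The article states both routes and the default class explicitly, and the objection is to what those statements say.

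**Conclusion.** The gap is real and narrow. As written, a patient with one nodule excised and benign (or biopsied benign without 12-month volumetry), and the others stable or resolved on 12-month volumetry, meets neither definite-benign route. The patient is at best probable benign and drops out of the definite-only analysis. The documents give no number affected; it is probably small, and the effect on the primary discharge comparison is probably slight. A material loss of primary power or a biased primary OR is not something the documents support. What matters more is the secondary outcomes: because exclusion depends on having had a procedure, excisions and 30-day procedure events in definite benign-nodule patients tend to be undercounted. This rests on the literal wording of Ground truth diagnosis and on some patients having more than one qualifying nodule, which Box 1 permits and the wording of both routes anticipates.

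**What to change.** Replace the two all-nodule routes with one per-nodule rule. A patient is benign when each qualifying nodule is shown benign by either accepted route: volumetric stability or resolution at 12 months, or benign histology within 12 months of the baseline CT. Keep malignant as at least one qualifying nodule. Among the six combinations tested, this moves only the mixed patient. If the full protocol or analysis plan already has such a rule, align the article with it.

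The cost is one sentence, settled before the analysis. The Data collection section already provides for follow-up images, research volumetry where a site does not use it is covered under Ground truth diagnosis, and biopsies, treatments and the final nodule diagnosis are recorded. No new data collection appears necessary.
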